### Results of pilot study

Sputa used for spiking tests were obtained from four patients who were not diagnosed with IPA. TAFC and bmGT were undetectable in these samples. The detected concentrations of the 5 ng/mL and 40 ng/mL TAFC and bmGT standards spiked into the sputa from the four no IPA patients are presented in Table 4. The method was found to be accurate and precise and has high recovery for both TAFC and bmGT from spiked sputum samples (Table 4). The accuracy (%deviation), precision (%RSD) and recovery (%) with our protocol for TAFC/bmGT detection at a 5 ng/mL level were ≤ ±5.0/5.0%, 5.2/7.3% and 98.4/96.9%, respectively.

**Table 4 Tab4:** Evaluation of accuracy, precision, and recovery of TAFC and bmGT from spiked sputum samples (mean ± SD)

Spiked TAFC & bmGT (ng/mL)	Detected TAFC (%deviation)	Detected bmGT (%deviation)	TAFC Recovery % (%RSD)	bmGT Recovery % (%RSD)
0	Not detected	Not detected	Not applicable	Not applicable
5	4.9 ± 0.3 (−1.6)	4.8 ± 0.4 (−3.1)	98.4 ± 0.1 (5.2)	96.9 ± 0.1 (7.3)
40	38.7 ± 1.2 (−3.3)	39.0 ± 2.9 (−2.5)	96.7 ± 3.0 (3.1)	97.5 ± 7.3 (7.4)

## Discussion

The clinical and radiological features of IPA are atypical, leading to the difficulty in an early diagnosis and treatment of the disease. There are still uncertainties and controversies associated with the diagnosis of IPA in clinical practice. Intensive efforts have been made to improve the diagnosis in “high-risk” individuals such as haematological and immunocompromised patients. Consequently, a series of approaches have been developed attempting to access a precise diagnosis.

Biomarker development has opened new possibilities in the diagnosis of a great number of disorders including IPA. Biomarkers related to IPA have been isolated and investigated largely in serum or BALF sample, yet few study has addressed the possibility of sputum biomarkers in the diagnosis of IPA. Each sample type has its advantages as well as disadvantages (Table 5). Biomarker detection using serum is convenient, inexpensive and time-saving, presenting high specificity [20], however the sensitivity was reported to be low in non-haematological patients [6, 23, 44, 45]. In comparison, BALF assays exhibit higher sensitivity as well as specificity in both neutropenic [46] and non-neutropenic patients [7, 9], probably because BALF is retrieved from local airways. However, the bronchoscopy is an invasive and costly procedure, and it might not be accessible to severe patients or those with contraindications.

**Table 5 Tab5:** Pros and cons of serum, BALF and sputum samples for IPA diagnosis in non-haematological patients

Samples	Pros	Cons
Serum	□Convenient, cheap and fast □High specificity	□Low sensitivity
BALF	□Local-infection related □High sensitivity and specificity	□Invasive, having contraindications □Expensive
Sputum	□Convenient, cheap and fast □Local-infection related □Non-invasive	□Affected by colonization and contamination

Sputum is the phlegm from the respiratory tract that has altered macromolecular, polymer composition and biophysical properties varying with diseases. Studies investigating sputum biomarkers are often limited by the techniques to obtain the specimen; however, intensive studies have demonstrated that hypertonic saline-induced sputum can be processed to yield reproducible results that reflect disease activity and correlate with BALF [47]. *Aspergillus*-related biomarkers, including *A*-DNA and GM, have been investigated using sputum samples, and we have developed a method to detect TAFC and bmGT in sputum; therefore, it is technically possible to use sputum for biomarker detection in the diagnosis of IPA.

Although no studies have investigated the superiority of the sputum assay over serum or BALF for the diagnosis of IPA in non-haematological patients, the sputum assay might be a valuable and useful approach for the detection of *Aspergillus* infection in patients with pre-existing respiratory diseases due to the following reasons. First, non-neutropenic patients tend to develop airway invasive forms of IPA [24, 25], which implies that airway-retrieved samples might be more sensitive to *Aspergillus* constituents. Additionally, Escribano et al. [48] identified matching genotypes of *Aspergillus fumigatus* in BALF and the sputum/bronchial secretion samples in proven or probable IPA patients, which indicates a comparable accuracy of BALF and sputum detection for the diagnosis of IPA. Furthermore, in the study by Kimura et al. [27], sputum GM was elevated in all patients with proven or probable IPA, and sputum GM showed a higher concentration (average GM index of 4.5) than that in BALF and serum (1.4 and 1.0, respectively). The above evidence strongly supports the usefulness of the sputum assay for the diagnosis of IPA.

Potential diagnostic biomarkers for IPA have been intensively studied, given the problem of an early diagnosis. We have reviewed the literature systematically to identify potential biomarkers that can be detected in a sputum sample. Galactomannan (GM) is a cell wall polysaccharide that is released by *Aspergillus* during fungal growth. The method of GM detection has been commercialized and widely used in the clinic with serum and BALF samples [19]. The serum GM assay exhibits low sensitivity (23.1–42%) for the diagnosis of IPA in non-haematological patients [6, 23], whereas BALF GM shows higher sensitivity and specificity [6–9]. The GM assay for sputum samples has been established in several studies (Table 1). Whether a GM assay based on lower airway derived sputum can be used as a non-invasive tool for the diagnosis of IPA deserves investigation. The measurement of GM in sputum might provide a more sensitive and non-invasive diagnostic approach for IPA.

GM detection can be affected by non-*Aspergillus* fungi and food that contains GM and beta-lactam antibiotics, which can produce false-positive values [49–51]. Several other biomarkers have been shown to play a role in the diagnosis of IPA and may be potential candidates for future clinical use. A rapid detection with LFD is an immunochromatographic assay that uses a monoclonal antibody called JF5 that targets an extracellular glycoprotein secreted during active fungal growth [36]. The test can be performed bedside and accomplished within 15 mins and, therefore, can be used as an early indicator for *Aspergillus* infection. The device is highly specific to antigens from *Aspergillus* but does not react with antigens from a large number of clinically important fungi, especially *Candida species* [36]. Pan et al. [52] conducted a meta-analysis to investigate its diagnostic accuracy for invasive aspergillosis, and showed that the LFD assay using BALF had higher sensitivity (86%) and specificity (93%) than serum (68% sensitivity and 87% specificity). Importantly, the BALF LFD assay also exhibited satisfying diagnostic performance for IPA (77% sensitivity and 92% specificity) in patients with URD [11]. Sputum supernatant has a similar matrix as BALF after processing procedures; hence, the use of the sputum LFD assay may provide a bedside and time-saving diagnostic tool for IPA.

TAFC is a siderophore secreted soon after conidiospore germination by *Aspergillus* in iron-limited media and is essential for fungal virulence [53, 54]. In a rat model of *Aspergillus fumigatus* infection, (68)Ga radiolabelled *Aspergillus* TAFC selectively accumulates in infected lung tissue [55]. Recently, Carrol et al. [37] detected TAFC in the serum of patients at risk for invasive aspergillosis using ultra-performance liquid chromatography tandem mass spectrometry. TAFC might be a potential early diagnostic biomarker for IPA. Gliotoxin (GT) is the major and the most potent toxin produced by *Aspergillus fumigatus* and mediates immunosuppressive and proapoptotic effects that may promote the establishment of invasive aspergillosis [56–58]; however, the rapid elimination of GT from body fluids by adjoining tissues and circulating cells precludes its feasibility as a biomarker for IPA [59–61]. bmGT is the inactive metabolite derived from GT and is quite stable after secreted, therefore it has been studied for the possibility of being an alternative biomarker [61]. Matxalen et al. [62] found that serum bmGT presented higher sensitivity (61.5%) and similar specificity (93%) compared to serum GM in haematological patients for the diagnosis of IPA. The assays for TAFC and bmGT have not yet been developed and validated in sputum. After a series of strict experiments, we first identified and standardized the TAFC and bmGT assays in sputum via the HPLC-MS/MS technique. We further validated the methods by determining the sputa induced from a group of patients with probable IPA or no IPA, which is consistent with the clinical diagnosis showing the great potential of being a non-invasive and useful marker for IPA. The detailed methods to process sputum and detect TAFC and bmGT in sputum have been submitted for patents (State Intellectual Property Office in China, No.201710428772.9). In this study, the diagnostic performance of sputum TAFC and bmGT assays for the diagnosis of IPA in patients with underlying respiratory disease will first be examined.

RT-PCR is a precise approach to detect *A*-DNA, and it has been applied for serum and BALF samples even though there is a lack of standardized protocol. Several meta-analyses [21, 63–67] assessed the efficacy of PCR assays on these two sample types for the diagnosis of IPA in haematological patients. The results showed that BALF PCR had much higher sensitivity (approximately 90%) and specificity (> 90%) than serum (85% for sensitivity and 75% for specificity). Several studies [28, 29, 68, 69] used PCR to identify *Aspergillus* in sputum and showed that sputum PCR had higher sensitivity than routine fungal culture; however, this technique has not been applied in the diagnosis of IPA and will be addressed in our study.

Sputum is a type of sample that is viscous and heterogeneous. To accurately detect biomarkers in sputum plugs, a proper processing method is needed. Dithiothreitol (DDT) is a commonly used reagent to homogenize sputum before all kinds of constituents are examined, and it is recommended for the pre-treatment of viscous samples by guidelines [70]. Baxter et al. [28] processed sputum with DDT and sonication before performing a GM assay and the results showed excellent GM reproducibility and low interassay and intraassay coefficients of variation. However, Prattes et al. [71] examined the effect of DDT on a BALF GM assay and found conflicting results. GM levels in BALF were substantially decreased from 0.51 ODI to 0.01 ODI after pre-treatment with DTT, and the LFD assay in BALF was also dramatically affected. Although this study targeted BALF, it is likely that DTT might affect sputum GM and LFD detection. Therefore, to minimize the effect of DTT on these biomarker assays, we will pre-treat sputum samples with phosphate buffered saline, which is in accordance with the method by Kimura et al. [27].

There are concerns about the specificity of the sputum assay related to colonization or contamination. Nevertheless, the four biomarkers (GM, JF5 antigen, TAFC, bmGT) in our study are produced and released during fungal growth. It is less likely that the increase in the levels of these biomarkers is a result of contamination of fungal spores. In addition, lower airway secretions will be used by sputum induction, and sputum quality control by squamous cell counting and viability calculation will further exclude the possibility of contamination. We will also determine an appropriate cut-off value of different sputum biomarkers, which will help to differentiate colonization from infection.

There are several highlights of this study. We systematically evaluate the validity of various biomarkers based on sputum from lower airways for the diagnosis of IPA for the first time; in particular, the establishment of a method that simultaneously detects TAFC and bmGT in sputum is first described and applied for patents and reported. Furthermore, the study population, i.e., patients with URD, has been increasingly recognized to present with IPA, which is associated with high mortality [12], but only has been addressed in a small number of studies. We assess the sputum biomarkers for IPA diagnosis in this population for the first time, and the results may help to provide novel, non-invasive and valuable diagnostic tools for IPA in patients with URD. In addition to sputum, serum and BALF will also be collected and compared for their diagnostic performance. In the statistical analysis, we will conduct two different analyses to investigate the impact of the possible IPA group on the interpretation of the results. Except for the investigation of diagnostic efficacy, we will also conduct a clinical follow-up to observe the prognosis of different types of IPA and further investigate host factors predisposing to IPA in patients with URD.

This study has some limitations that should be considered. The categories of probable and possible IPA are proposed for immunocompromised patients only in the consensus report by the EORTC/MSG. However, this report recognizes that the revised definition of IPA does not necessarily apply to immunocompetent patients as it is difficult to find a sufficient basis for identifying appropriate host factors. Patients with URD may possess much different risk factors to *Aspergillus* infection compared to those immunocompromised individuals. As in the study by Prattes et al. [11], pre-existing respiratory disease is added as an independent host factor to establish the diagnosis in our study. We will also conduct post hoc analyses of the host factors linked to diagnosis and prognosis for further investigation. The concentration of biomarkers in the sputum may fluctuate with the production and expectoration of the sputum and the releasing of the biomarkers from the infection site. However, this study already includes a great number of biomarkers from different sample types with a comparable large sample size, and we do not perform serial tests for sputum biomarkers at different time points across the disease course, which may lead to the underestimation of the diagnostic performance of several biomarkers. Further study may be warranted to investigate the dynamic variation of different *Aspergillus* biomarkers in sputum.

In conclusion, the design and protocol of a clinical trial that investigates the performance of sputum signatures for the diagnosis and prognosis of IPA in patients with URD are presented here. The results of this innovative study are expected to provide answers to the following questions. Are sputum signatures valuable diagnostic tools for IPA in patients with URD? Which signature is the strongest potential candidate? Would the modified host factors be appropriate for this patient population? What disease course of IPA would present in this population? The study findings will provide evidence and novel insights into these areas, which have not been accessed.

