## Methods/design

### Study design

This is a prospective diagnostic trial. The study protocol has been registered with the Chinese Clinical Trial Registry (ChiCTR-DPD-16009070). Participants will be enrolled from respiratory wards and intensive care units in the West China Hospital, Sichuan University of China. Inclusion criteria are patients (1) with URD including chronic pulmonary diseases (COPD, asthma, lung cancer, bronchiectasis, interstitial lung diseases, and cystic fibrosis) and acute pulmonary diseases (bacterial pneumonia, viral pneumonia, and acute bronchitis); (2) willing to provide informed consent; and (3) able to tolerate sputum induction. Exclusion criteria are patients (1) with underlying haematological malignancies; or (2) that are previous receipts of solid organ transplant; or (3) that are unable to produce sputum.

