### Diagnostic criteria

The diagnostic criteria of IPA are based on the 2008 EORTC/MSG framework [17]. Host factors, clinical criteria and mycological criteria to establish the diagnosis of IPA in this study population are listed in Table 2. In accordance with the study by Prattes et al. [11], URD is added as one of the host factors. We propose to make this modification due to several reasons. Host factors of the diagnostic criteria in previous guidelines were originally defined for haematological patients but have not been validated in non-neutropenic patients. Additionally, those typical host factors promoted by EORTC/MSG are frequently absent in non-haematological patients [2, 23]. Patients will be classified into proven, probable, possible and no IPA groups according to the revised 2008 EORTC/MSG criteria [17] (Table 3).

**Table 2 Tab2:** The diagnostic framework for IPA in patients with URD

Host factors	Recent history of neutropenia (< 0.5 × 10^9^ neutrophils/L for > 10 days) temporally related to the onset of infection Prolonged use of corticosteroids at a mean minimum dose of 0.3 mg/kg/day of prednisone equivalent for > 3 weeks Treatment with immunosuppressants during the past 90 days Inherited severe immunodeficiency Underlying respiratory diseases including chronic pulmonary diseases (COPD, asthma, lung cancer, bronchiectasis, interstitial lung diseases, and cystic fibrosis) and acute pulmonary diseases (bacterial pneumonia, viral pneumonia, and acute bronchitis)
Clinical criteria	The presence of 1 of the following 3 signs on chest computed tomography: Dense, well circumscribed lesion(s) with or without a halo sign Air-crescent sign Cavity on chest computed tomography
Mycological criteria	Cytologic or microscopic evidence of *Aspergillus* elements or recovery of *Aspergillus* in sputum or BALF Positive GM test in serum or BALF

**Table 3 Tab3:** IPA classification according to revised 2008 EORTC/MSG criteria

Proven IPA	Histopathological or cytopathological examination of lung tissue showing *Aspergillus* hyphae from needle aspiration or biopsy specimen with evidence of associated tissue damage, OR positive culture result for *Aspergillus* from a sample obtained by sterile procedure from the lung.
Probable IPA	Host factors, AND clinical criteria, AND mycological criteria
Possible IPA	Host factors AND clinical criteria
No IPA	Other cases excluded from proven, probable and possible IPA groups

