### GM detection

Peripheral venous blood will be collected into Vacutainer® tubes (BD Worldwide, Suzhou, China), and serum will be obtained by centrifugation at 3000 rpm, 4 °C for 10 mins. The GM assay on serum, BALF and sputum will be performed with the Platelia *Aspergillus* enzyme immunoassay (Bio-Rad, California, USA) according to the manufacturer’s instructions. Tests for serum and BALF GM will be considered positive at cut-off values of ≥0.5 ODI and ≥ 1.0 ODI, respectively.

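### A beta-lactam false positive shared by reference GM and sputum GM can create cases that sputum GM scores as hits, tilting the sensitivity comparison towards it

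*Protocol article*

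**What the plan says.** - **Interference.** The Discussion states that "GM detection can be affected by non-*Aspergillus* fungi and food that contains GM and beta-lactam antibiotics, which can produce false-positive values". It uses this only to motivate the other markers.
- **Reference standard.** Table 2 (Diagnostic criteria) lists "Positive GM test in serum or BALF" as one way to meet the mycological criterion. Table 3 defines probable IPA as "Host factors, AND clinical criteria, AND mycological criteria". Underlying respiratory disease is both an inclusion criterion and a host factor, so every participant meets the first element.
- **Index test.** Under GM detection: "The GM assay on serum, BALF and sputum will be performed with the Platelia" kit. PCR, TAFC, bmGT and the lateral flow device use other targets or methods.
- **Population.** Patients come from respiratory wards and intensive care units. Eligible diseases include "acute pulmonary diseases (bacterial pneumonia, viral pneumonia, and acute bronchitis". None of the three exclusion criteria concerns antibiotics. The only drug-timing rule, under Participants screening and recruitment, concerns antifungals.
- **Analysis.** Statistical analysis compares assays by McNemar test in two analyses that differ only in how possible IPA is handled. The Discussion closes by asking "Which signature is the strongest potential candidate".

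**The concern.** Take a patient with a CT sign, no Aspergillus infection and no other mycological evidence. A drug-induced positive serum or BALF GM makes this patient a probable case. If the same drug also turns sputum GM positive, sputum GM is credited with a true positive. A marker unaffected by the drug is correctly negative but is scored as a miss.

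Both planned analyses keep this patient as a case, so neither can reveal the problem. The sputum GM cut-off is also read from ROC curves built on these cases. At stake is one of the study's closing questions: an apparent sensitivity advantage of sputum GM could partly reflect antibiotic exposure.

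**Working it through.** **The plan's own figure.** The plan gives no figure on interference. Its case number, 59, comes from Sample size calculation: a = 1.414 × Φ⁻¹(0.795) = 1.165; V = 0.0099 × exp(−a²/2) × (6a² + 16) = 0.1213; n = 1.96² × 0.1213 / 0.09² = 57.5, so 58 against the stated 59. This agrees closely, and the present point does not affect it.

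**Formula.** Let s be the true sensitivity, equal for sputum GM and a comparator. Let f be the share of reference cases that are false through GM interference, q the sputum GM positivity among those false cases, and p the comparator's false-positive rate.

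- Apparent sensitivity of sputum GM = (1 − f)s + fq
- Apparent sensitivity of comparator = (1 − f)s + fp
- Gap = f(q − p), above zero whenever q > p

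**Illustration; every input is assumed.** There are 50 true cases and 60 CT-positive patients without IPA, 60% of them on beta-lactams; s = 80%, p = 10%. A share r of the exposed has a false-positive reference GM. False cases = 60 × 0.6 × r. Sputum GM sensitivity = (40 + q × false cases)/(50 + false cases). Comparator sensitivity = (40 + 0.1 × false cases)/(50 + false cases).

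| r | False cases | Comparator | Sputum GM, q = 100% | Gap | Sputum GM, q = 50% | Gap |
|---|---|---|---|---|---|---|
| 5% | 1.8 | 77.6% | 80.7% | 3.1 | 79.0% | 1.4 |
| 10% | 3.6 | 75.3% | 81.3% | 6.0 | 78.0% | 2.7 |
| 20% | 7.2 | 71.2% | 82.5% | 11.3 | 76.2% | 5.0 |

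**Effect on the McNemar test.** This was simulated with 59 reference cases, s = 70%, p = 15% and 20,000 runs per setting (all assumed except the 59). With f = 5%, 10% and 20%, the test declares sputum GM better in 7%, 14% and 39% of trials at q = 90%, and in 4%, 6% and 13% at q = 50%. With no excess sputum positivity (q = p) the figure is about 2.5%.

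**Controls without a CT sign.** These are classed as no IPA whatever their GM result, so a false reference GM does not change their status. A false-positive sputum GM in them is counted as a false positive, which is correct.

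**The case against.** **This is mainly an omission.** A journal article may leave recording of concomitant drugs to the full protocol, and the other interferents the Discussion names (food, other fungi) act by the same path. Both points stand: the absent data field alone would be no finding, and beta-lactams are one route into the wider overlap between reference GM and sputum GM. But the reference rule, the shared assay, the exclusions and the two-analysis structure are fixed in this document and leave the route open.

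**Joint positivity is assumed.** The Discussion speaks of GM detection in general and shows no interference in sputum. Sputum plugs are suspended in 8 volumes of buffer, the reference cut-offs are 0.5 ODI (serum) and 1.0 ODI (BALF), and the sputum cut-off is still to be set from the data. A marginal serum result need not imply a positive sputum result. This stands. At half concordance the gaps more than halve, and sputum GM sensitivity drops below its true 80%, though the comparator drops further. Even at full concordance, the smallest gap is under two patients in about 52 cases.

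**Stronger readings.** A reader might infer that reduced sputum GM specificity in exposed controls is a second distortion. It is not: that loss belongs to the assay in the population enrolled. A reader might also infer that every accuracy measure favours sputum GM. That is unsupported, because the specificity loss works against it and the net effect on AUC can go either way.

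**Conclusion.** The point holds as a bias in the sensitivity comparison, and so in any ranking resting on it, towards sputum GM. It is conditional on beta-lactams turning both reference and sputum GM positive in the same patient more often than the comparator is falsely positive, and on the comparator not sharing the interference. Proven cases, and probable cases with culture or microscopy evidence, do not depend on GM and are unaffected.

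The size cannot be derived from the documents. That exposure is common is an inference from the eligible diseases and wards. The gaps of 1.4 to 11.3 points are illustrations and should not be read as estimates. The point merits an inexpensive change to the analysis; it does not invalidate the design.

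**What to change.** 1. Record beta-lactam exposure at the time of sputum, serum and BALF sampling, taken from the medical record.
2. In Statistical analysis, prespecify sputum marker accuracy by exposure.
3. Also prespecify a sensitivity analysis of the head-to-head comparison that excludes patients whose only mycological evidence is GM obtained under beta-lactam exposure, or that uses a reference without GM.
4. State any claim that sputum GM outranks another marker together with whether it holds in these analyses.

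The patients removed in step 3 should be left out and not relabelled as possible IPA. The second planned analysis counts possible IPA as non-IPA, so true cases with positive sputum GM would become false positives and sputum GM would be penalised by construction. The same care applies to patients who drop to possible under a GM-free reference. Exclusion also removes some true cases, so step 4 asks for the result to be reported and does not make it a pass-or-fail condition.

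The cost is one extra data field, plus fewer cases and wider intervals in the sensitivity analysis. Patient care is unchanged.

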### Sample size calculation

GM is the most studied biomarker for the diagnosis of IPA among our candidate signatures; therefore, the sample size calculation is based on the diagnostic accuracy of the sputum GM assay reported by previous studies. Receiver operating characteristics (ROC) curves show the trade-off between sensitivity and specificity, and the area under the curve (AUC) is considered as an overall index of accuracy for quantitative biomarkers. The sample size estimation is based on AUC reported previously [27].

With 95% confidence (*α* = 0.05) to guarantee the marginal error of estimate (i.e. the difference between true AUC and its estimate) does not exceed from a pre-determined value of d = 0.09, and expecting an equal number of diseased and non-diseased cases, the required sample size for each group is:1$$ \mathrm{n}=\frac{{\mathrm{z}}_{\frac{\alpha }{2}}^2\ \mathrm{V}\left(\hat{\mathrm{AUC}}\right)}{d^2} $$

V($$ \widehat{\mathrm{AUC}} $$) denotes the variance of $$ \widehat{\mathrm{AUC}} $$ that is estimated parametrically based on binormal assumption [41, 42]. This binormal assumption is chosen because our study implements a four-category rating scheme (i.e. proven IPA, probable IPA, possible IPA and no IPA). $$ \mathrm{V}\left(\widehat{\mathrm{AUC}}\right) $$ is calculated as follows:2$$ \mathrm{V}\left(\widehat{\mathrm{AUC}}\right)=\left(0.0099\times {e}^{\raisebox{1ex}{$-{a}^2$}\!\left/ \!\raisebox{-1ex}{$2$}\right.}\right)\times \left(6{a}^2+16\right) $$

where a = *φ*^−1^(AUC) × 1.414 and *φ*^−1^ is the inverse of standard cumulative normal distribution. With a pre-specified AUC of 0.795 according to Kimura et al. [27], the required sample size for each group is 59 after above calculation. Therefore, we will recruit a minimum number of 118 participants with 59 controls (no IPA) and 59 cases (proven or probable IPA).

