### Statistical analysis

The data will be analysed with SPSS 22.0 software (IBM Corp, Armonk, NY, USA). Two analyses will be performed based on the IPA classification, one in which patients with possible IPA will be excluded in the calculation and a second analysis in which patients with possible IPA will be classified as not having IPA. Therefore, the comparisons and analyses will be (1) proven/probable IPA versus no IPA, and (2) proven/probable IPA versus possible/no IPA [43]. The sensitivity, specificity, negative predictive value (NPV), positive predictive value (PPV), and diagnostic odds ratio, including 95% confidence intervals, will be calculated for different biomarkers. ROC analysis will be performed and AUC (including 95% CI) and cut-off values will be established from the ROC curves for GM, RT-PCR, TAFC and bmGT. The McNemar χ^2^ test will be used to compare sensitivity, specificity, NPV, and PPV between different assays. The difference in hospital stay and the survival between possible or no IPA versus proven or probable IPA will be analysed with chi-square tests, and the relationships between the levels of biomarkers and the hospital stay and survival will be analysed via regression models. *P* < 0.05 will be defined as statistically significant.

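### Cut-offs are set and accuracy is estimated in the same patients, and a strongest marker is to be named, with no selection rule and no correction for optimism

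*Protocol article*

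**What the plan says.** All of this is in the protocol article.

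- **Statistical analysis:** "AUC (including 95% CI) and cut-off values will be established from the ROC curves for GM, RT-PCR, TAFC and bmGT". Sensitivity, specificity, NPV, PPV and the diagnostic odds ratio are calculated for the biomarkers in the study patients. The only stated comparison between assays is the McNemar test on sensitivity, specificity, NPV and PPV.
- **GM detection, and A-DNA extraction and RT-PCR:** Fixed positivity thresholds are given for serum and BALF GM but not for sputum GM. Sputum PCR is called positive or negative by a cut-off still to be determined from the recorded cycling thresholds.
- **LFD performance:** LFD is read as test line present or absent, so it has no ROC curve. It is a fifth sputum candidate.
- **Sample size calculation:** The AUC is described as an overall accuracy index for quantitative markers. The study is sized so that the error in one AUC, that of sputum GM, "does not exceed from a pre-determined value of d = 0.09". The result is a minimum of 59 cases and 59 controls.
- **Discussion:** The closing questions include "Which signature is the strongest potential candidate". Elsewhere the derived cut-offs are expected to help separate colonization from infection. The limitations mention possible underestimation of performance, because there is no serial testing, but no source of overestimation.

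**The concern.** Two uses of the same data push the reported accuracy upward. First, a cut-off chosen to perform well on a sample fits that sample's chance features, so sensitivity and specificity at that cut-off, measured in the same sample, are optimistic. This affects every quantitative marker. Second, the marker that comes out on top is partly the one that was lucky in these patients, so its figures carry a further upward shift that an ordinary CI ignores. This is bias in an estimate and is separate from multiplicity in the pairwise tests.

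At stake are the accuracy and threshold attached to the marker named as strongest, which a later study would naturally take as its starting point.

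**Working it through.** **1. The plan's own figure.** Inputs from Sample size calculation: "With a pre-specified AUC of 0.795", d = 0.09, 95% confidence, equal groups, and a variance "estimated parametrically based on binormal assumption".

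- a = 1.414 × Φ⁻¹(0.795) = 1.165
- V = 0.0099 × exp(−a²/2) × (6a² + 16) = 0.1213
- n = 1.96² × 0.1213 / 0.09² = 57.5, so 58 per group

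The stated 59 is reproduced to within rounding of the inputs: an AUC of 0.79 gives 58.3, so 59. At 59 per group the half-width is 1.96 × √(0.1213/59) = 0.089. This is the precision of one AUC for a marker fixed in advance.

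**2. Simulation of the plan as written.** The setting was 59 cases and 59 controls, four equal-variance binormal markers, empirical AUC with a DeLong Wald 95% CI, cut-off at the maximum Youden index, top marker = highest observed AUC, and 4000 runs per scenario. The article gives neither the between-marker correlations nor the true AUCs of the markers other than GM, so both are assumed and varied. The Youden rule is also assumed.

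| True AUCs | Correlation | Top AUC too high by | 95% CI coverage | Lower limit above truth | Sens + spec too high by |
|---|---|---|---|---|---|
| all 0.795 | 0 | 0.041 | 83.0% | 17.0% | 0.138 |
| all 0.795 | 0.5 | 0.031 | 86.9% | 13.1% | 0.122 |
| all 0.795 | 0.7 | 0.025 | 88.6% | 11.3% | 0.113 |
| all 0.795 | 0.9 | 0.015 | 91.1% | 8.6% | 0.097 |
| 0.82/0.795/0.795/0.77 | 0 | 0.036 | 83.9% | 16.1% | 0.129 |
| 0.82/0.795/0.795/0.77 | 0.5 | 0.025 | 87.8% | 12.1% | 0.110 |
| 0.85/0.795/0.75/0.70 | 0 | 0.016 | 90.1% | 9.8% | 0.093 |
| 0.85/0.795/0.75/0.70 | 0.5 | 0.007 | 92.2% | 7.1% | 0.078 |
| 0.85/0.795/0.75/0.70 | 0.7 | 0.002 | 93.3% | 5.8% | 0.070 |

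For a marker fixed in advance, AUC bias was about 0 and coverage 93% to 95%, but sensitivity plus specificity at its own cut-off was still 0.065 to 0.074 too high.

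**3. Splitting the accuracy optimism.** With equal markers and correlation 0, 0.072 of the 0.138 (52%) comes from the cut-off and 0.066 from selection. At correlation 0.9, 0.074 of 0.097 (76%) comes from the cut-off. The cut-off is therefore half or more of the problem and applies to all four markers.

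**4. Why the interval misses.** With equal markers the mean CI width is 0.144 to 0.154, against 0.160 for a pre-fixed marker, so it is only 3% to 10% narrower. Almost every miss has the lower limit above the truth, so the fault is mainly the centre.

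**5. Against the planned margin.** 0.041/0.09 = 46%, 0.025/0.09 = 28% and 0.002/0.09 = 2%.

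**6. Does a bootstrap help?** In two separate simulations at correlation 0.5, repeating selection and cut-off derivation in each resample cut the AUC bias from 0.029–0.034 to 0.008–0.013 (equal markers) and from 0.020–0.021 to 0.003–0.004 (close markers). One of the two also gave 0.005 to 0.003 with one clear winner, and cut the optimism in the Youden index from 0.127, 0.108 and 0.073 to 0.045, 0.031 and 0.023 (equal, close, clear winner). Coverage of a corrected interval was not simulated.

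**The case against.** A reader might infer that the trial will pick its winner by AUC, present that AUC as the main result, and so report an invalid CI that is too narrow. The documents do not support that reading. No selection rule is stated, the only between-assay comparison is McNemar on accuracy measures, and the binary LFD also competes. The anchor sentence is one of four closing Discussion questions and speaks of a potential candidate. All four AUCs are to be estimated, and each is essentially unbiased if no marker is singled out. GM, on which the study is sized, is fixed in advance. When one marker is clearly best and the markers are correlated, the AUC bias is close to zero. When the bias is largest the markers are equal, so choosing the wrong one costs little.

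It can also be said that a condensed article may leave optimism correction to an analysis plan that is not shown. That is fair, and the point is not that a detail is absent. It is that the procedure the article does state, followed as written, gives optimistic figures.

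These objections limit the AUC claim and make it conditional. They do not touch the cut-off optimism, which needs no winner and affects every quantitative marker. Choosing the strongest marker on observed sensitivity or specificity would reuse the same patients too, although the figures above apply only to selection by AUC.

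**Conclusion.** The point holds in a limited form and is best labelled a cheap improvement.

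- **Firm:** setting cut-offs and measuring accuracy in the same 59 + 59 patients overstates sensitivity plus specificity by about 0.07 for any one marker under a Youden-type rule, and by about 0.10 to 0.14 for the top marker when markers are similar.
- **Conditional:** if strongest means highest AUC, that AUC is too high by about 0.00 to 0.04 and its nominal 95% CI covers about 83% to 93%. Narrowness of the interval is a minor part of this.

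The sizes depend on assumed AUCs, correlations, binormality and the Youden rule. They are for the 59 + 59 minimum and for cases against no-IPA controls. The second planned analysis, which adds possible IPA to the controls, was not simulated.

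**What to change.** In Statistical analysis:

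1. State how the strongest marker is decided, for example the highest AUC among the four quantitative markers, with LFD compared on sensitivity and specificity. State the rule that sets each cut-off.
2. For every quantitative marker, correct sensitivity and specificity at the derived cut-off by a patient-level bootstrap, stratified by case and control, with the cut-off re-derived in each resample.
3. For the marker named strongest, also repeat the selection in each resample. Report the corrected and uncorrected AUC, with an interval shifted by the estimated optimism.
4. Describe that marker's figures and cut-off as exploratory until validated in new patients.

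The cost is wording and a short program, possibly in a package other than the SPSS 22.0 named in the article. No further patients or samples are needed. Headline figures will be slightly lower. Some bias remains: up to about 0.013 in the AUC with equal markers, and 0.023 to 0.045 in the Youden index. When one marker is clearly best, the corrected AUC is marginally noisier (root mean squared error 0.044 against 0.041 in one simulation). Bonferroni intervals over the four AUCs are not a substitute. With z = 2.498 the half-width at 59 per group rises to 0.113, and keeping 0.09 would need 94 per group. They also leave the upward bias in place.
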